### Recruitment – public housing developments and residents

#### Recruiting public housing developments

Developments are eligible for selection as one of our study sites if they have at least 100 units. A statistician conducted the randomization stratified by management company (Boston Housing Authority/Private) using a computer program, such that 3 developments went to the E group, 3 developments went to the I group, 3 developments went to the E+I group, and 3 developments went to the control.

#### Recruitment and screening of the evaluation cohort

We propose to recruit 50 participants per development in the evaluation cohort. Eligibility criteria include being able to speak English or Spanish, being 18 years old or older, being a public housing resident from one of our study sites, not planning to move within the next 2 years, having access to a phone, not currently participating in another physical activity study, being able to walk independently without regular need for special equipment (wheelchair, scooter, or walker), ability to provide informed consent, and willingness to complete the accelerometer-based device measurement. By design, the entire cohort will be low-income.

Recruitment will take place at the developments, using common sampling rules and a direct household door-knocking approach [39–41]. Trained Research Assistants will approach units based on an assigned list and will attempt to identify an eligible resident using a brief script. The survey steps will be as follows: approach the unit, attempt to identify a resident, describe the study, determine eligibility, collect informed consent documents, collect the survey measurements, explain the physical activity device, and remind the residents of follow-up visits. Data collection documents for screening, documenting informed consent, and baseline, 12- and 24-month assessments are stored in REDCap [42].

### Intervention overview: role of the HLA

In all intervention developments, community health workers (termed Healthy Living Advocates or HLAs in this program) serve as intervention delivery agents and have been a successful way to partner with public housing communities for engagement activities and clinical trials [35, 43–45]. HLA training consists of 4 sessions (mix of in-person and Zoom) covering study overview and HLA responsibilities; information about importance of physical activity and influences on physical activity; data management and study protocol; culturally appropriate engagement; how to lead walking groups and adverse events. HLAs also participate in the hospital’s CPR/first aid program. At the conclusion of the training, HLAs undergo an evaluation and are provided with feedback on responding to safety-related situations, proficiency with engagement, and alternative exercises. Once proficiency has been reached, HLAs are able to lead activity sessions independently. HLAs are in frequent communication with each other and monthly with study investigators to discuss progress in each development and issues as they arise in the developments and with residents. At all meetings, HLAs will exchange ideas for engaging residents and strategize about problems that they are having in their work.

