**Methods:**

The study design is a prospective, cluster randomized controlled trial, with housing developments (*n=*12) as the units of randomization. In a four-group, factorial trial, we will compare an environmental intervention (E) alone (3 developments), an individual intervention (I) alone (3 developments), an environmental plus individual (E+I) intervention (3 developments), against an assessment only control group (3 developments). The environmental only intervention consists of community health workers leading walking groups and indoor activities, a walking advocacy program for residents, and provision of walking maps/signage. The individual only intervention consists of a 12-week automated telephone program to increase physical activity motivation and self-efficacy. All residents are invited to participate in the intervention activities being delivered at their development. The primary outcome is change in moderate intensity physical activity measured via an accelerometer-based device among an evaluation cohort (*n=*50 individuals at each of the 12 developments) from baseline to 24-month follow up. Mediation (e.g., neighborhood walkability, motivation) and moderation (e.g., neighborhood stress) of our interventions will be assessed. Lastly, we will interview key informants to assess factors from the Consolidated Framework for Implementation Research domains to inform future implementation.

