##### Structured walking groups

HLAs will organize walking groups and adjust scheduling around work and childcare commitments of participants. Groups will begin meeting twice weekly and will occur more frequently as participation increases. The main recruitment strategies employed for these groups will be from flyers, from tables with posterboard displays, and by word-of-mouth referrals. Flyers will be distributed in a variety of ways including door-to-door, posting in high traffic areas, placing in mailboxes, and distributing at community events. Walk group participants will gather at a meeting place, such as a community room, within their development. Children are welcome to attend the walks with their parent/guardian to promote family participation and because improvised day care is not sustainable in the long run. Well behaved pets are also invited. All walking sessions will begin with light stretching. The groups then proceed with their walks. After each walk, they return to the meeting place for a post-walk stretching session. In case of inclement weather, all public housing developments have access to a large group room where they will lead indoor exercise classes, such as dance classes like Zumba or dances to upbeat popular music like Soca.

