HLAs will facilitate access to the Phone2Health program for residents who live in developments randomized to receive the I and E+I intervention. The HLAs will obtain verbal informed consent from interested residents and set them up to use the telephone program by entering their phone number, preferred call days/times, and preferred language into a study-specific website. During enrollment, participants will indicate specific times and days they would like to be contacted. If a call is missed, the system will call back 15 minutes later. If that call is missed, the system will call on the second preferred day. After 2 weeks of missed calls, the HLA will contact the participant to troubleshoot any issues the participant is having (e.g., missed calls). Once completed, residents could re-enroll in the 12-week program if they wish to.

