#### Process measures

Process measures will be evaluated to monitor implementation of the intervention and to document receipt of the intervention. The HLAs will fill out a checklist after each physical activity event or promotion activity of the Phone2Health program. This information will help investigators determine intervention dosage and process. Specific metrics will include: 1) reach: the number of people who completed HLA walks/physical activity sessions or engaged in Phone2Health program; 2) the dose of the intervention: the number of HLA activities delivered and completed Phone2Health calls; and 3) participants’ feedback and perceptions of the intervention activities.

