##### Statistical analysis

To examine this hypothesis, we exploit our study design which has a multifactorial design embedded in a cluster randomized controlled trial. Multifactorial experimental designs combine the rigor of experimental design with the ability to produce results on the effectiveness of alternate approaches to multicomponent interventions in a single experiment. We will use multilevel regression analysis and test for an interaction effect between the environmental and individual level interventions (E+I). The presence of a significant interaction between E and I on the primary outcome of physical activity suggests synergy between these components of the intervention. If the effects of the environmental level intervention and individual level intervention are additive there should not be a significant interaction in the model. In this case, we can compare the interaction results to the multilevel intervention group (E+I) to examine the exploratory hypothesis that E+I is more effective than E&I combined.

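### E, I and E+I share a community health worker that control lacks, so the E-by-I interaction is net of any shared worker effect, and I versus control is not the effect of the automated calls alone

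*Protocol article*

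**What the plan says.** **Who delivers what.** Under the heading on the role of the HLA: "In all intervention developments, community health workers (termed Healthy Living Advocates or HLAs in this program) serve as intervention delivery agents". All HLAs receive the same four-session training.

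- E and E+I: "HLAs will organize walking groups and adjust scheduling around work and childcare commitments of participants". HLAs also hand out the trail maps (Walking trails and maps).
- I and E+I: "HLAs will facilitate access to the Phone2Health program for residents who live in developments randomized to receive the I and E+I intervention". They take verbal consent and enter residents' details, and "After 2 weeks of missed calls, the HLA will contact the participant to troubleshoot any issues the participant is having".
- Process measures shows that HLAs also promote the phone programme: "The HLAs will fill out a checklist after each physical activity event or promotion activity of the Phone2Health program".
- Control is assessment only (Abstract; Design of the Community Walks study). No HLA activity is described there.

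**How the I arm is labelled.** The Abstract says: "The individual only intervention consists of a 12-week automated telephone program to increase physical activity motivation and self-efficacy". HLAs are not mentioned in that description.

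**HLA support as a cause.** Table 1 lists support from HLAs among the mediators, measured at all three assessments, and Aim 2 analyses it as a mediator of physical activity.

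**How the interaction will be read.** Hypothesis 3 sets the E+I gain against the sum of the E-versus-control and I-versus-control gains. Its analysis section takes a significant interaction, with no sign given, as suggesting synergy. It then adds: "If the effects of the environmental level intervention and individual level intervention are additive there should not be a significant interaction in the model".

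**The concern.** To read a 2×2 as a test of two components, each component must be switched on by one factor only. Here an HLA comes with either factor and is missing only when both are off. The plan also treats HLA support as something that may change activity, so it cannot be assumed inert when the interaction is interpreted.

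Two conclusions are exposed. The first is Hypothesis 3: overlap between the packages through the shared worker pulls the interaction down, so a null result could be read as additive phone and environmental components when it is not evidence of that. The second is I versus control: a positive result could be credited to an automated call that needs no staff, although it was obtained with an on-site worker promoting the programme, enrolling residents and following them up. The Discussion says the trial should show which interventions are important drivers of activity and inform decisions on components, so attribution matters to its users.

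**Working it through.** The plan states no figure for this point, so there is none to reproduce. The check is algebra on the four arm means.

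**Notation.** e = environmental effect and i = phone effect, each including the HLA tasks that belong only to that package; s = synergy; h = the part of the HLA effect common to E, I and E+I that counts once in E+I. Relative to control:

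- Control = 0
- E = e + h
- I = i + h
- E+I = e + i + s + h

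**Contrasts.**

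- Interaction = (E+I) − E − I + control = (e + i + s + h) − (e + h) − (i + h) + 0 = **s − h**
- I versus control = **i + h**; E versus control = **e + h**
- E+I versus E = **i + s**; E+I versus I = **e + s**

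An intercept, two main effects and one interaction already use up the four arm means. h would be a fifth quantity, so arm comparisons cannot separate it from s at any sample size.

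**When HLA effects differ by arm.** With HLA effects hE, hI and hEI, the interaction is s + hEI − hE − hI. Two assumed cases:

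- Effects that add up, (hE, hI, hEI) = (2, 2, 4): bias = 4 − 2 − 2 = 0.
- Effects that overlap, (3, 1, 3): bias = 3 − 3 − 1 = −1.

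Only overlap biases the interaction downward.

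**Scale, for illustration only.** The documents give no h; 0 to 5 minutes is assumed, because 5 minutes is the between-group difference in the Sample size section. For an interaction size, the LMS paragraph is borrowed: 3.75 at 85% power, two-sided 0.05. It was written for moderation, gives no SD or ICC, and its normal-approximation standard error is 3.75 / (1.960 + 1.036) = 1.25.

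| Assumed h | Expected interaction if s = 3.75 | Chance of a significant positive interaction if s = 3.75 | Chance of a significant negative interaction if s = 0 |
|---|---|---|---|
| 0 | 3.75 | 85% | 2.5% |
| 1 | 2.75 | 59% | 12% |
| 2 | 1.75 | 29% | 36% |
| 3 | 0.75 | 9% | 67% |
| 3.75 | 0 | 2.5% | 85% |
| 5 | −1.25 | not computed | not computed |

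The table shows the direction and how the error grows with h. It does not estimate h.

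**The case against.** **The tasks differ by arm.** HLAs lead walks under E and handle promotion, consent, set-up and missed calls under I; E+I combines all activities of both. Most HLA work may therefore simply add up, in which case it belongs to e and i and does no harm. This stands. The bias is confined to the overlapping part, which could be small because the HLA role in the I arm is light.

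**Hypothesis 3 compares packages.** It is defined through arm contrasts, so E and I can be read as packages as delivered, and overlap through a shared worker is then genuine sub-additivity. This also stands. A reader might infer that the additivity sentence is false. It is true for packages; it fails only when carried over to the phone and environmental components themselves.

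**HLA exposure is already measured.** Checklists, adherence indices and the mediator scale are planned. They help to describe exposure, but HLA support is not randomised, so they do not separate h from s without further assumptions.

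**The I-arm label is abstract shorthand.** The body does disclose HLA delivery in the I arm, so nothing is hidden. The short description is still the one most likely to be carried into the report of results.

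**Hypothesis 2 might seem to rescue the component effects.** A reader might infer that, because h cancels, E+I versus E isolates the phone programme and E+I versus I the environmental programme. It does not: those contrasts equal i + s and e + s, and each still includes the HLA work that comes with the added package.

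**Conclusion.** The point holds as a limit on interpretation. The randomised comparisons of packages under Hypotheses 1 and 2 remain valid. Two readings need restricting: what the E-by-I coefficient says about the components, and what I versus control says about the automated calls.

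The error equals h in each: −h in the interaction and +h in I versus control taken as the phone effect. This assumes that control has no HLA (inferred from its assessment-only description, which nothing contradicts) and that part of the HLA effect is common to the active arms and not additive in E+I. The direction against synergy further assumes that HLA contact raises activity. The size is unknown.

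A reader might go further and conclude that the factorial design is invalid, or that the interaction is biased by the whole HLA effect. The documents do not support either: HLA tasks are largely specific to the arm, and effects that add up leave the interaction unbiased.

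One defect does not depend on h. The text lets any significant interaction suggest synergy, although a negative one points the other way.

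**What to change.** 1. In the Hypothesis 3 analysis section, state that the E-by-I coefficient compares the packages as delivered and is net of any effect of the shared HLA; that only a positive coefficient supports synergy; and that a null or negative coefficient is not evidence that the phone and environmental components themselves are additive or lack synergy.
2. Describe the I arm, including in the Abstract, as Phone2Health delivered with HLA outreach. Report I versus control as the effect of that package.
3. Describe E+I versus E, and E+I versus I, as the effect of adding one package, with its HLA tasks, on top of the other. Do not present either as the effect of a component by itself.

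The cost is wording only, with no new data, staff or randomisation. The downside is that a null interaction can no longer be claimed as component additivity, and I versus control becomes a package effect.

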### Intervention overview

#### Environmental level intervention: improving the walkability of the public housing development environment

These activities aim to change multiple aspects of the housing development to enable walking as an easy, natural part of life. Our IRB determined that informed consent is not required of people who join environmental-level activities.

##### Walking trails and maps

WalkMassachusetts, a non-profit walkability and pedestrian safety advocacy organization serving the Commonwealth of Massachusetts, will mark walking trails surrounding each of the intervention developments with signage indicating walking trail status, duration, directions, and distance. There will be at least one short (15-20 min), one medium (25-30 min), and one longer (40-45 min) trail in each E and E+I development neighborhood, to accommodate walkers of various levels. HLAs will distribute maps of the walking trails and other highlights at every walk, at community events, and in the development’s management office. In addition to the walking trails, maps contain brief tips about physical activity and are available in both English and Spanish.

##### The process of developing the walking routes

Neighborhood walkability (obtained by assessment using the MAPS tool section 2.7.1) plus feedback from meetings with the managers, local community meetings, and the HLAs with lived experience in these neighborhoods, was used to inform the construction of the walking routes, and subsequent maps created by a professional graphic designer. These walking routes are designed to be used in the E and E+I intervention developments. With authorization from the City of Boston, wayfinding signage will be placed on poles and free-standing displays to instruct HLAs to accompany the walking routes illustrated on the maps.

##### Structured walking groups

HLAs will organize walking groups and adjust scheduling around work and childcare commitments of participants. Groups will begin meeting twice weekly and will occur more frequently as participation increases. The main recruitment strategies employed for these groups will be from flyers, from tables with posterboard displays, and by word-of-mouth referrals. Flyers will be distributed in a variety of ways including door-to-door, posting in high traffic areas, placing in mailboxes, and distributing at community events. Walk group participants will gather at a meeting place, such as a community room, within their development. Children are welcome to attend the walks with their parent/guardian to promote family participation and because improvised day care is not sustainable in the long run. Well behaved pets are also invited. All walking sessions will begin with light stretching. The groups then proceed with their walks. After each walk, they return to the meeting place for a post-walk stretching session. In case of inclement weather, all public housing developments have access to a large group room where they will lead indoor exercise classes, such as dance classes like Zumba or dances to upbeat popular music like Soca.

##### Advocacy training meetings

Leaders at WalkMassachusetts will host a 2-session advocacy training meeting at least once per year in each E and E+I development for the HLAs and interested residents. Residents will receive a $25 gift card for attending. The topics covered will be how to: evaluate the walkability of their neighborhood, report issues with sidewalks and other pedestrian infrastructure, and elevate issues to city officials, state agencies, and other advocate groups. Short-term results of this advocacy training could include cleaning up the development, restriping pavement markings, and installing pedestrian signage. Long-term changes might result from calling for city officials to improve sidewalks, adding trees, benches, incorporating complete street designs and traffic calming measures. Residents will know of and be able to connect with WalkMassachusetts for ongoing advocacy support after the training.

#### Individual level intervention: automated ehealth phone program for physical activity

Phone2Health is based upon a previously tested telephone program designed to increase physical activity among urban African American adults [46] and was further modified to meet the needs of public housing residents (see section 2.3). Phone2Health is a 12-week automated telephone-based program, consisting of sessions lasting 10 minutes or less, available in English and Spanish. Enrolled participants will receive one call per week for 12 weeks with a goal of increasing motivation and self-efficacy for physical activity. The calls will include conversations that speak to participants using computer-controlled speech. The calls are user friendly and interactive where participants can respond to conversations by pressing keys on their phone’s keypad. Each week various barriers and recommendations are addressed through several sections of the call. Each week the call starts with a brief physical activity assessment to assess the participants current level of physical activity. Participants' level of physical activity will be based on the previous week's goal and their ability to meet or exceed that goal. The call moves into a counseling section where participants are given feedback from their assessment, information and tips on physical activity, and the benefits of incorporating physical activity into their lifestyle. Topics addressed in this section may include injury prevention, identifying support systems, or discovering different types of physical activity. Following the counseling section is goal setting, where each week participants set a new and achievable goal such as adding an additional day of physical activity during the week. Changes to goals are monitored by the system and the program will suggest an adjustment if the participant has chosen to increase the goal by a large amount or to decrease their goal. The call ends with a call summary and upbeat concluding statement, such as an inspirational quote. The program utilizes a “call-out” mechanism in which registered users receive a weekly call at a predetermined time and day.

HLAs will facilitate access to the Phone2Health program for residents who live in developments randomized to receive the I and E+I intervention. The HLAs will obtain verbal informed consent from interested residents and set them up to use the telephone program by entering their phone number, preferred call days/times, and preferred language into a study-specific website. During enrollment, participants will indicate specific times and days they would like to be contacted. If a call is missed, the system will call back 15 minutes later. If that call is missed, the system will call on the second preferred day. After 2 weeks of missed calls, the HLA will contact the participant to troubleshoot any issues the participant is having (e.g., missed calls). Once completed, residents could re-enroll in the 12-week program if they wish to.

